#### Secondary outcomes

Secondary endpoints will be analyzed using linear regression models adjusting for baseline values and stratification factors. Changes in symptoms over time for dyspnea, fatigue, cognitive impairment (“brain fog”), and post-exertional malaise will be analyzed with McNemar’s test. Changes in symptom severity over time will be analyzed descriptively. A per protocol analysis is done for all secondary outcomes similar to the one described for the primary outcome.

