### Objectives {7}

The primary objective of this randomized controlled trial (RCT) is to investigate the effects of Pycnogenol® versus placebo on self-reported health status (primary outcome) in people with PCC.

Secondary objectives are to assess the efficacy of Pycnogenol® versus placebo on PCC-related symptoms (e.g., fatigue, post-exertional malaise, dyspnea, cognitive function), health-related quality of life, symptoms of depression and anxiety, functional exercise capacity, physical activity, and biomarkers for inflammation, oxidative stress, coagulation, and endothelial function.

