#### Secondary outcomes

All secondary outcomes are assessed at baseline (V2) and after 12 weeks (V4), except post COVID-19 related symptoms. Symptoms are assessed using online questionnaires prior to study visits (V1, V2, V4) and a symptom diary that is completed on a weekly basis between the baseline and 12-week visit.

*Post COVID-19 symptoms* are assessed using self-reported surveys prior to the screening visit (V1), baseline visit (V2), and end of intervention (V4) [1, 3, 11]. Participants complete a symptom diary on a weekly basis including severity grading.

*Fatigue* is assessed using the 13-item Functional Assessment of Chronic Illness Therapy—Fatigue Scale (FACIT-Fatigue) [33]. A cut-off score of < 34 will be used for descriptive analysis, and norm values from a German population [34] will be used for comparisons. The scale is responsive to treatment, and triangulated MIDs have been established for various patient populations [35]. In a small study (*n* = 32) with people attending COVID-19 rehabilitation, the MID for the FACIT-Fatigue scale has been estimated between 2.7 and 3.6 points [36]. This estimate will be used for the interpretation of between-group differences in this study.

*Dyspnea* is assessed using the Chronic Respiratory Questionnaire (CRQ) dyspnea domain [37–39]. The CRQ dyspnea domain consists of five questions rated on a 7-point scale. The instrument is valid, reliable, and responsive, with a reported MID of 0.5 units [40], which will be used to interpret between-group differences.

*Cognitive function* is assessed by trained personnel using the German version of the Montreal Cognitive Assessment (MoCA) test. The MoCA test is commonly used to evaluate cognitive function in people with COVID-19 and PCC [41–44], with a cut-off score < 26 for impairment [42, 45]. The standard correction for years of education will be applied.

*Anxiety and depression* are assessed with the Hospital Anxiety and Depression Scale (HADS) [46–48]. The scale includes 14 questions with a 4-point Likert-type scale. It is a valid and reliable instrument with a triangulated MID of 1.5–1.7 units change [30, 49, 50]. A cut-off value of 7 or higher will be used to report the number of participants with depression and/or anxiety [51].

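### Post-exertional malaise is named in a versus-placebo objective, but its only specified analyses are a within-person McNemar test and a description of severity

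*Protocol article*

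**What the plan says.** Objectives {7} words the secondary aim as a comparison of arms: "efficacy of Pycnogenol® versus placebo on PCC-related symptoms (e.g., fatigue, post-exertional malaise, dyspnea, cognitive function", followed by further outcomes. Post-exertional malaise is one of the four symptoms named there.

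The paragraph on secondary outcomes in Statistical methods {20a} gives three rules in sequence:

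- A general one: "Secondary endpoints will be analyzed using linear regression models adjusting for baseline values and stratification factors".
- A specific one for the presence of four symptoms over time (dyspnea, fatigue, brain fog and post-exertional malaise), ending "post-exertional malaise will be analyzed with McNemar’s test".
- One for grading: "Changes in symptom severity over time will be analyzed descriptively".

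Outcomes {12} lists what is measured. Fatigue has the "13-item Functional Assessment of Chronic Illness Therapy—Fatigue Scale (FACIT-Fatigue" scale, dyspnea has the CRQ dyspnea domain, and cognition has the MoCA. For the FACIT-Fatigue minimal important difference the article says "This estimate will be used for the interpretation of between-group differences in this study", and it makes a matching statement for the CRQ. For post-exertional malaise no scale is listed. The data can come only from the symptom surveys at V1, V2 and V4 and from the diary: "Participants complete a symptom diary on a weekly basis including severity grading".

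**The concern.** The objective asks whether symptoms differ between Pycnogenol and placebo. McNemar's test asks whether the proportion with a symptom differs between two time points in the same people. Run within each arm, it gives two separate before/after results. Run on both arms pooled, it ignores treatment altogether. Neither form estimates or tests a treatment effect.

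The distinction matters here because change is expected without any drug effect. Background {6a} reports that symptom burden and severity improved over time in the investigators' own cohort. Eligibility {10} requires at least one of the four symptoms at screening, so some regression to the mean is also likely. A significant before/after result in the Pycnogenol arm would therefore be weak evidence about the product, and setting a significant result in one arm beside a non-significant one in the other is not a valid comparison of arms.

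What is at stake is one named symptom, post-exertional malaise, together with the yes/no symptom data from the surveys.

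**Working it through.** **Step 1. Which symptoms have a specified between-arm analysis?**

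| Symptom in the objective | Scale listed in Outcomes {12} | Adjusted regression in {20a} | McNemar in {20a} |
|---|---|---|---|
| Fatigue | FACIT-Fatigue | yes | yes |
| Dyspnea | CRQ dyspnea domain | yes | yes |
| Cognitive function | MoCA | yes | yes (brain fog) |
| Post-exertional malaise | none | no | yes |

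The last row has only the within-person test, plus description of severity.

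**Step 2. Arm size.** Sample size {14} gives 68 per group from a difference of 8, an SD of 16.5 and 80% power. Two-sided 0.05 is assumed because that section states no alpha. The normal formula is n = 2(1.960 + 0.842)² × (16.5/8)² = 2 × 7.849 × 4.254 = 66.8, so 67 per arm. The t-test version gives 67.75, so 68. The stated figure reproduces, and 68 per arm is used below.

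**Step 3. What McNemar's test sees.** Let b be the number in an arm who lose the symptom and c the number who gain it. The exact p-value is min[1, 2 × P(X ≤ min(b, c))], with X binomial(b + c, ½). Treatment does not enter.

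Example: with 20% losing and 5% gaining, the expected counts in 68 people are 13.6 and 3.4. Take b = 14 and c = 3 in both arms. Then p = 2 × (1 + 17 + 136 + 680)/2¹⁷ = 1,668/131,072 = 0.013 in each arm, while the between-arm difference in change is exactly zero.

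**Step 4. Rejection rates with no drug effect.** The same transition probabilities apply in both arms. The share gaining the symptom is 5% throughout. All these rates are assumptions, since the article gives no 12-week rate. The rejection rate r is obtained by summing over all values of b and c for n = 68, and for n = 136 when the arms are pooled. Because the arms are independent, the chance of significance on Pycnogenol but not on placebo is r(1 − r).

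| Share of arm losing the symptom | r, Pycnogenol arm | Pooled | Pycnogenol only, r(1 − r) |
|---|---|---|---|
| 10% | 11% | 25% | 0.108 × 0.892 = 10% |
| 15% | 36% | 70% | 0.361 × 0.639 = 23% |
| 20% | 65% | 94% | 0.652 × 0.348 = 23% |
| 25% | 85% | 99% | 0.852 × 0.148 = 13% |
| 30% | 95% | over 99.9% | 0.949 × 0.051 = 5% |

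The last column is the misleading direction only. Counting either arm doubles it, to 46% at 15%, but half of those trials favour placebo.

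**Step 5. A direct comparison for contrast.** In each arm let d = (b − c)/68 and v = [(b + c)/68 − d²]/68, and test z = (d₁ − d₂)/√(v₁ + v₂) against 1.96. In simulation under the same null scenarios this rejects in about 5% of trials across the whole range.

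**The case against.** A reader might infer from the McNemar sentence that the symptom objective as a whole receives no between-arm comparison. The article does not support that: three of the four named symptoms have a scale that falls under the baseline-adjusted regression rule, and the FACIT-Fatigue and CRQ thresholds are explicitly to be applied to differences between groups.

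A reader might also infer that the investigators intend to read a significant within-arm result as efficacy, or to compare significance across arms. The article says neither. It applies McNemar's test to change over time, which is a question the test does fit, and it does not say whether the test is run per arm or pooled. Step 4 therefore shows what such a reading would cost; it does not predict how the results will be reported.

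The transition rates are open to challenge as well. They apply to the whole arm, yet not everyone need have post-exertional malaise. If half did (an assumption), 20% of the arm losing it means 40% of those affected recovering in 12 weeks, which is a lot. The 10% row corresponds to 20% of those affected and is the gentler case.

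Describing the weekly severity grades is a legitimate choice for one of many secondary measures. A longitudinal model would use the data better, but its absence is not an error.

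Finally, a statistical analysis plan that is not shown may add a between-arm estimate. That is possible, but this is not a detail left open: the article names the test. Nor does the general regression rule clearly rescue post-exertional malaise, because the sentences that follow it assign symptom presence and severity their own methods. If both were meant to apply, the text needs to say so.

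**Conclusion.** The point holds in a narrow form. For post-exertional malaise, which the objective names, the article specifies no between-arm comparison. For the survey presence of the other three symptoms the same gap exists, but their scales cover the underlying question.

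Under assumed loss of 10% to 30% and gain of 5%, with no drug effect, 68 per arm and two-sided 0.05, McNemar's test is significant in the Pycnogenol arm in 11% to 95% of trials. Pooled, the range is 25% to over 99.9%. It is significant on Pycnogenol alone in 5% to 23%. The direction of the argument does not depend on these rates, because the test has no treatment term whatever they are; only the size does.

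The primary EQ-VAS analysis is a proper adjusted comparison of arms and is untouched. This should be fixed before unblinding, but it is not a flaw in the trial's main inference.

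**What to change.** For each of the four symptoms, specify a logistic regression of presence at 12 weeks on treatment, baseline symptom status and the two stratification factors. Report an adjusted odds ratio or risk difference with a 95% confidence interval. Keep McNemar's test, if wanted, as within-arm description, and state that it is not used to judge efficacy. A between-arm ordinal or mixed model for the weekly severity grades is optional.

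The cost is a few sentences of analysis wording and modest extra programming. The surveys and diary already supply the data. Because the section on non-adherence and missing data {20c} commits the team to report and justify any substantial departure from the plan, the change should be recorded as a dated amendment before the allocation codes are opened.

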#### Other outcomes

Using baseline data, we aim to investigate associations between objectively measured physical activity, symptom burden and severity, functional exercise capacity, and quality of life. Descriptive statistics and regression models will be applied.

### Interim analyses {21b}

Interim analyses are not planned.

### Methods for additional analyses (e.g., subgroup analyses) {20b}

We will conduct a per-protocol analysis comparing adherent versus less-adherent participants. Adherence is assessed by calculating the percentage of taken/unused study products over the course of the study. We will compare groups of participants who took ≤ 70% of capsules versus those who took > 70% of capsules during the study to investigate any potential effect of adherence on primary and secondary outcomes.

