### Strategies to improve adherence to interventions {11c}

To enhance the validity of our data and adherence to study products, we planned a short study visit six weeks and two phone calls two respectively 9 weeks after randomization (Fig. 1) to stay in close contact with study participants. During the phone calls, the importance of adhering to the study products and monitoring symptoms in the diary is discussed. Study products returned at the follow-up visits (V3, V4, Fig. 1) are counted and recorded in the database. In addition to the intention-to-treat analysis (primary analysis), we plan a per protocol analysis based on adherence to study products and investigate its potential impact on primary and secondary outcomes.

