## Statistical methods

### Statistical methods for primary and secondary outcomes {20a}

#### Primary outcome

The primary analysis will be done following the intention-to-treat (ITT) principle. All randomized participants having received at least one dose of Pycnogenol® will be included in this analysis. We will use multivariable linear regression models to compare EQ-VAS values at 12 weeks adjusted for baseline values and stratification factors, i.e., PCC duration (≤ 6 months versus > 6 months) and presence of any chronic disease(s).

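### The analysis labelled per-protocol compares participants by capsule intake (>70% versus ≤70%) instead of comparing Pycnogenol with placebo, so it cannot show whether the product works when taken

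*Protocol article*

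**What the plan says.** The section Methods for additional analyses {20b} of the Protocol article defines the analysis: "We will conduct a per-protocol analysis comparing adherent versus less-adherent participants". It then fixes the two groups, "We will compare groups of participants who took ≤ 70% of capsules versus those who took > 70% of capsules during the study", and the purpose, "to investigate any potential effect of adherence on primary and secondary outcomes". Treatment arm appears in neither sentence.

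Two other places mention a per-protocol analysis. Strategies to improve adherence {11c} sets it beside the intention-to-treat analysis: "we plan a per protocol analysis based on adherence to study products and investigate its potential impact on primary and secondary outcomes". The Secondary outcomes paragraph of Statistical methods {20a} says: "A per protocol analysis is done for all secondary outcomes similar to the one described for the primary outcome". The Primary outcome paragraph just before it describes no per-protocol analysis. It gives only the intention-to-treat model, used to "compare EQ-VAS values at 12 weeks adjusted for baseline values and stratification factors".

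The Objectives {7} state the question of the trial: to "investigate the effects of Pycnogenol® versus placebo on self-reported health status (primary outcome) in people with PCC".

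**The concern.** A per-protocol analysis normally keeps the comparison of assigned arms and restricts who enters it. The rule in {20b} changes the comparison itself, from assigned arm to capsule intake. Intake is measured after randomisation and chosen by the participant. Someone who feels worse, has side effects or notices no benefit may take fewer capsules of either product. The primary model's baseline adjustment, if it carries over, cannot remove confounding that arises during the 12 weeks, and {20b} names no adjustment for determinants of adherence.

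No other section restores the randomised contrast. The only per-protocol analysis that the article defines therefore does not address the trial's objective, for the primary outcome or for the secondary outcomes to which it is extended. Its label may lead readers to take it as evidence about the product.

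**Working it through.** **Inputs from the article.** SD 16.5, target difference 8 units, 80% power, 68 per group (136 in total), 150 with drop-out (Sample size {14}); MID 8 (Outcomes {12}); 1:1 allocation (Trial design {8}); 70% cut-off ({20b}).

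**Assumptions, because the article gives no figure.** Two-sided alpha 0.05; share p at or below 70% intake of 10-30%; correlation ρ between intake and 12-week EQ-VAS of 0.1-0.4; correlation r between baseline and 12-week EQ-VAS of 0.5-0.7.

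**Step 1: the plan's own figure.** A two-sample t-test for 8 units with SD 16.5 at 80% power needs 67.75 per arm, so 68 per arm and 136 in total. This matches. With 10% added, 136 × 1.10 = 149.6, or 150. The planning inputs are sound and can be reused.

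**Step 2: expected intake contrast with an inert product.** Treat intake and outcome as jointly normal and cut intake at its p-th quantile z. The expected high-minus-low difference is

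ρ × SD × φ(z) / [p(1 − p)].

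For p = 20%, φ(z) = 0.280 and p(1 − p) = 0.16. At ρ = 0.3 this gives 16.5 × 0.3 × 0.280 / 0.16 = 8.7 units. Across p = 10-30%:

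| ρ | Expected difference, unadjusted (units) |
|---|---|
| 0.1 | 2.7-3.2 |
| 0.2 | 5.5-6.4 |
| 0.3 | 8.2-9.7 |
| 0.4 | 10.9-12.9 |

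It reaches 8 at ρ of about 0.25-0.29.

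**Step 3: with baseline adjustment.** The SD becomes 16.5 × √(1 − r²), and ρ is now the correlation with the residual outcome. At r = 0.5 the SD is 14.3 and the difference reaches 8 at ρ of 0.29-0.34. At r = 0.7 the SD is 11.8 and ρ must be 0.35-0.41. At ρ = 0.1-0.2 the adjusted difference is about 2.0-5.6 units.

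**Step 4: simulation.** N = 136, r = 0.5, inert product, intake unrelated to arm, 4,000 runs per setting, p = 10-30%:

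| Residual ρ | Mean intake contrast (units) | Trials at 8 or more | Trials with p < 0.05 |
|---|---|---|---|
| 0 | about 0 | 0.2-2.9% | about 5% |
| 0.2 | 4.7-5.6 | 11-28% | 28-43% |
| 0.3 | 7.1-8.4 | 36-53% | 53-77% |

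In the same setup, Pycnogenol versus placebo among participants above 70% intake has a mean difference of −0.04 to 0.07, and p < 0.05 in 4-6% of trials.

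**Step 5: an active product.** The article does not say whether the intake contrast pools the arms. If it does, and intake is equal by arm, half of the high-intake group is on placebo. A true 8-unit benefit confined to high-intake Pycnogenol participants would appear as 8 × 1/2 = 4 units, before any confounding. So the contrast can understate as well as overstate.

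**The case against.** The strongest reply is that this is a supplementary analysis. The article makes intention-to-treat primary and lists the intake comparison under additional analyses. It states an aim about adherence, and no decision rule uses the result. All of that stands, and it limits the seriousness. It does not repair the label: the article calls this contrast per-protocol and offers no other. A separate analysis plan may define it differently, but the article's own wording would then need correcting.

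Three stronger readings are tempting and unsupported.

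- A reader might infer that the result would be presented as support for efficacy. No section says so. The stated aim is an effect of adherence, so misreading is a risk of the label and not a plan.
- A reader might infer that an MID-sized artefact is to be expected. It depends on assumed correlations. With 20% at or below 70% intake and r = 0.6, the adjusted difference averages only 4.6-7.0 units at ρ of 0.2-0.3. The article also ties the MID of 8 to the comparison of intervention with placebo, not to an intake contrast.
- A reader might infer that the contrast measures nothing but confounding. That holds only for an inert product.

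It is also fair to say that the arm comparison among high-intake participants is selected after randomisation. The 4-6% in Step 4 follows from assuming that intake does not depend on arm. The article itself lists gastrointestinal discomfort as the most frequently reported treatment-related side effect ({11b}), so that assumption could fail.

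**Conclusion.** The point holds in limited form. The contrast that the article calls per-protocol is non-randomised and post-baseline, and it cannot answer whether Pycnogenol works when taken. That conclusion comes from the text and needs no assumption about size. The size figures in the working are illustrative: they rest on the assumed share of low intake, the assumed correlations and the joint-normal model, and the correlation needed to reach 8 units is moderate, not trivial. A contrast made within each arm would still be confounded, although the placebo arm would then offer a check. Because the primary estimate, its interpretation and the sample size do not change, this is a correction that should be made, not one on which the trial's validity depends.

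**What to change.** Before unblinding:

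1. Define the per-protocol analysis as Pycnogenol versus placebo, with the primary adjusted linear model, restricted in both arms to participants who took more than 70% of capsules. Use the same restriction and arm contrast for the secondary outcomes.
2. State its limits. It selects after randomisation and is unbiased only if adherence does not depend on arm. With 10/20/30% excluded from 68 per arm, about 61/54/48 remain, and power for 8 units falls from 80% to about 76/71/66% (normal approximation, no gain from baseline adjustment).
3. Report adherence by arm, so that readers can judge that assumption.
4. Relabel the >70% versus ≤70% contrast as exploratory and non-causal.
5. Align sections {11c}, {20a} Secondary outcomes and {20b}, and supply the primary-outcome description to which {20a} refers.

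A complier-average estimate, if wanted, belongs among the sensitivity analyses. Its exposure must be having taken more than 70% of assigned Pycnogenol, set to zero for everyone on placebo, with the assumption of no effect at 70% intake or below stated. Using arm as the instrument for taking more than 70% of any capsules would fail: both arms take capsules on the same schedule, so arm need not predict that exposure.

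The cost is wording and a few lines of code. Capsule returns are already counted at both follow-up visits (Other outcomes).

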### Methods in analysis to handle protocol non-adherence and any statistical methods to handle missing data {20c}

Substantial deviations from the original statistical plan will only be done if necessary due to unforeseen circumstances. Any such deviation will be reported and justified in the final report and the resulting manuscript(s). Missing follow-up data of study participants who did not conduct assessments at the final study visit (V4) will be imputed using multiple imputation by chained equations. The results from this procedure will be compared to the ones from the complete case analysis.

### Plans to give access to the full protocol, participant-level data and statistical code {31c}

We plan to deposit an anonymized dataset within available repositories (e.g., Dryad, Zenodo) to facilitate open access for other researchers. The study consent form will explicitly inform participants about the reuse and sharing of anonymized data. Identifiable information will not be shared with anyone outside of the research team. The statistical code will be made available in the publications.

